# Cancer@Work — a nurse-led, stepped-care, e-health intervention to enhance the return to work of patients with cancer: study protocol for a randomized controlled trial

**DOI:** 10.1186/s13063-016-1578-8

**Published:** 2016-09-15

**Keywords:** Cancer survivors, Employment, Return to work, E-health, Psycho-oncological care, Study protocol, Randomised controlled trial

## Abstract

**Background:**

Although the importance of work for patients with cancer is nowadays more acknowledged both in the literature as well as in cancer survivorship care, effective interventions targeting the return to work of these patients are still scarce. Therefore, we developed a nurse-led, stepped-care, e-health intervention aimed at enhancing the return to work of patients with cancer. The objective of this study is to describe the content of the intervention and the study design used to evaluate the feasibility and (cost) effectiveness of the intervention.

**Methods:**

We designed a multi-centre randomised controlled trial with a follow-up of 12 months. Patients who have paid employment at the time of diagnosis, are on sick leave and are between 18–62 years old will be eligible to participate. After patients have signed the informed consent form and filled in the baseline questionnaire, they are randomly allocated to either the nurse-led, stepped-care, e-health intervention called Cancer@Work, or care as usual. The primary outcome is sustainable return to work. Secondary outcomes are sick leave days, work ability, work functioning, quality of life, quality of working life and time from initial sick leave to full return to work without extensive need for recovery. The feasibility of the Cancer@Work intervention and direct and indirect costs will be determined. Outcomes will be assessed by questionnaires at 3, 6, 9 and 12 months of follow-up.

**Discussion:**

The results of this study will provide new insights into the feasibility and (cost) effectiveness of Cancer@Work, a nurse-led, stepped-care, e-health intervention for cancer patients aimed at enhancing their return to work. If proven effective, the intention is to implement the Cancer@Work intervention in usual psycho-oncological care.

**Trial registration:**

NTR (Netherlands Trial Registry): NTR5190. Registered on 18 June 2015.

## Background

In the last decades, the survival rates of cancer have improved significantly for most cancer types [1]. For that reason, a growing number of cancer survivors of working age are now able to remain in or return to work. However, a considerable number of patients with cancer still experience difficulties getting back to work [2] or they become unemployed [3] due to, for instance, cancer-related side effects or an insensitive work environment [4]. It is important to diminish these adverse work outcomes for patients with cancer, as work is both a key aspect of cancer survivorship and is also associated with higher levels of quality of life in these patients [5].

Although the importance of work for patients with cancer is nowadays more acknowledged both in the literature as well as in cancer survivorship care, interventions that are primarily aimed at enhancing return to work of cancer patients are still scarce [6]. In the past few years, a few studies reported results of an intervention primarily aimed at enhancing the return to work of cancer patients [6–8]. These studies reveal that it is feasible to deliver a work support intervention during cancer care that is highly appreciated by patients [7, 9]. However, these work support interventions need improvement, as most did not show effectiveness on return to work [9].

Most work support interventions for patients with cancer have been delivered to all patients in the same manner [6, 10]. Nevertheless, it is known that patients widely differ both in the number and type of work-related problems they experience upon their return to work [11] as well as in the duration from initial sick leave to sustainable return to work [12]. These differences indicate that a stepped-care intervention, in which the intensity of the intervention is tailored to the patients’ needs, might be more effective and efficient. Such a tailored intervention may lead to more effective return-to-work outcomes.

Previous studies on cancer and work have taught us three main things. First, self-assessed work ability is an important prognostic factor for return to work, irrespective of clinical characteristics [7, 13]. This finding has led to the hypothesis that return to work is influenced by patients’ expectations and beliefs regarding return to work and that addressing misconception or improving someone’s self-efficacy would enhance return to work [13]. A successful approach to increase someone’s self-efficacy is the involvement of self-management interventions [14] which might be based on cognitive behavioural techniques [15] or problem-solving techniques [15, 16]. Second, both employers and colleagues as well as cancer care providers are important stakeholders in the return to work of patients with cancer [11]. It has appeared difficult to connect with the workplace from the hospital [17], but a successful approach to solve this problem might be the use of integrative-care management [18]. Third, the longer the duration of sick leave, the more difficult it is to return to work [19]. Addressing return to work in an early phase during cancer treatment might therefore be the window of opportunity. Moreover, two studies showed that cancer patients appreciated receiving information on their return to work during early cancer treatment [8, 17]. For these reasons, we choose to develop an early intervention based on the theory of self-management and integrative-care management.

Numerous studies have demonstrated that e-health is a suitable way of delivering self-management interventions for various conditions, including cancer [20, 21], and to deal with various problems, including return to work [22, 23]. In addition, e-health proved suitable for delivering an integrative-care management intervention as well [24]. Based on these findings, we choose to deliver the intervention as an e-health intervention. We define e-health as the process of providing the intervention partly over the Internet including interaction with health care providers.

### Objective

The first objective of this paper is to describe the content of Cancer@Work, a nurse-led, stepped-care, e-health intervention aimed at enhancing the return to work of patients with cancer. The second objective is to present the study design aimed at evaluating the Cancer@Work intervention in terms of feasibility and (cost) effectiveness.

## Method

### Content of the Cancer@Work intervention

The Cancer@Work intervention has been developed based on a non-systematic review on the use of and compliance with e-health interventions, a non-systematic review on cancer and work and on semi-structured interviews with experts, cancer survivors, occupational physicians and supervisors. Development of the nurse-led, stepped-care, e-health intervention Cancer@Work has been described extensively elsewhere [25].

The Cancer@Work intervention is an e-health intervention blended with care from a specialised nurse of the treating hospital or another care provider (e.g. social worker), depending on the local setting. For readability we will refer to this care provider as a specialised nurse. The specialised nurse will (1) answer questions, (2) monitor and supervise use of the Cancer@Work intervention, (3) provide personal feedback on assignments of the Cancer@Work intervention and (4) encourage patients to comply with the intervention. To be able to blend their care with the Cancer@Work intervention, specialised nurses have access to a special section of the e-health intervention with which they are able to (1) see whether patients have used the Cancer@Work intervention, (2) see which functionalities each patient has used, (3) evaluate the content of some of the assignments, (4) answer questions from patients, (5) send messages to patients and (6) receive support from and answers to questions from an oncological occupational physician.

The intervention comprises two steps. Whether or not the intervention goal was met with step 1 is measured based on two indicators assessed by the specialised nurse: (1) no return to work and/or (2) problems experienced upon returning to work. If either indicator is affirmative, patients will enter step 2.

### Step 1: Information and advice in the Cancer@Work intervention and integrative-care management

The focus of step 1 is to deliver patient-tailored information on cancer and work with the help of the Cancer@Work intervention and to address misconceptions on cancer and work. Functionalities of the Cancer@Work intervention include assignments to create insight and to stimulate patients to take action on the following topics: (1) possible financial consequences of sick leave, (2) rights and obligations according to the Dutch social security system when sick-listed (tailored to the patient’s situation, i.e. a fixed versus temporary employment contract), (3) individual importance of work and (4) return-to-work plan. Furthermore, the Cancer@Work intervention includes a library with background information and a self-test to create awareness of the abilities to return to work and to restructure cognitions. The library includes, for instance, information on work adjustments, social support and legal and insurance issues, and it is conveniently arranged and has a search function. Additionally, patients can learn from former patients by means of advice, answers to frequently asked questions and the documentary ‘Irrevocable’ on experiences of cancer survivors upon returning to work. Patients are also able to keep a diary and to have a look at assignments that they have previously made. Finally, the Cancer@Work intervention offers patients the ability to send private messages to their specialised nurse. Following a patient’s first login, a welcome text and an instruction video explaining how to use the e-health intervention will be available.

Integrative-care management implicates the involvement of the patient’s supervisor, occupational physician and general physician. To accomplish this, the patient will be encouraged to invite his/her supervisor, occupational physician and/or general physician to use a public website, specially developed as part of the e-health intervention, containing information on cancer and work for supervisors, occupational physicians and general physicians (http://www.kanker-werk.nl/). When a patient invites his supervisor, occupational physician and/or general physician, they will receive an email with a short explanation of the aim of the Cancer@Work intervention. Once a patient has invited his supervisor, occupational physician or general physician, the Cancer@Work intervention offers the ability to send private messages to the stakeholder whom the patient has invited.

### Step 2: Problem solving in extended Cancer@Work intervention

The main functionality of the second step is a self-management assignment based on the problem-solving technique and blended care. Patients themselves actively work on their problem with the aid of the Cancer@Work intervention and the additional support of their specialised nurse. The ultimate goal is to create a strategy to manage the patient’s problems that inhibit a successful return to work. The self-management program is split into three assignments. First, patients formulate problems and opportunities regarding work. Second, patients formulate solutions for work-related problems. Third, patients generate a plan to execute the chosen solutions with regard to return to work. During this process their specialised nurse will provide personalised feedback after each assignment (online or face-to-face), monitor and supervise the progress and encourage patients to comply with the intervention.

#### Conditions of use

There is no prescribed use of the Cancer@Work intervention in terms of length, frequency or duration. Patients themselves decide when to use the Cancer@Work intervention and which content to use. They will go through the Cancer@Work intervention at their own pace and move from step 1 to step 2 if indicated. The Cancer@Work intervention will be available for 12 months.

#### Enhancing compliance

Every month a standardised email will be sent to patients as a reminder of the functionalities of the Cancer@Work intervention, if patients gave permission for these emails. These reminders intend to increase compliance with the intervention. Additionally, patients can ask their specialised nurse for personal coaching at any time during availability of the Cancer@Work intervention.

#### Privacy and support for the Cancer@Work intervention

For technical questions only, patients are able to contact the researcher by email. All patients are registered by the researcher and receive a unique username and password (changeable later). Patients are able to log in to the secured webpage by use of their unique username and password; then verification by text message will take place. The patient’s specialised nurse is able to view their profile and provide personalised feedback.

### Study design to evaluate the intervention Cancer@Work

For the description of the design of our evaluation study, we used the items of the CONSORT statement [26] as well as the SPIRIT checklist [27, 28] for improving the quality of reporting randomised trials.

### Organisation study

The design of this study is a non-blinded, multi-centre, randomised controlled trial with a follow-up of 12 months. An overview of consent, screening, enrolment, intervention, timing of measurements and data collection is shown in Fig. 1. The study will be conducted at the following hospitals from various geographical regions in the Netherlands: Academic Medical Center, Albert Schweitzer Hospital, Reinier de Graaf Groep, Flevoziekenhuis, the Antoni van Leeuwenhoek Hospital and Ter Gooi Hospital. The intervention group will receive the nurse-led, stepped-care, e-health intervention Cancer@Work, and the control group will receive care as usual, which is standard psycho-oncological care. The medical ethics committee of the Academic Medical Center approved the study and the conduction of the study at all participation hospitals. The board of management of the above-mentioned participating hospitals advised positively about local feasibility. Patients will sign an informed consent form before participating.

**Fig. 1 Fig1:**
[figure not shown]
Schedule of enrolment, intervention and assessments

### Recruitment of study population

The treating physician or nurse will check each patient’s eligibility at the outpatient clinic a few weeks after the first cancer treatment, which consists in most cases of surgery. The treating physician or nurse will inform all eligible patients about the study and will ask for consent to be contacted by the researcher. After telephonic contact by the researcher, the researcher will include patients in the study if they are willing to participate and after they have provided the signed informed consent form. Thereafter, the patient will be randomised to either the intervention group or to the control group. Patients who meet the eligibility criteria but are not willing to participate will be asked if they are willing to answer a few questions by telephone about their work situation at baseline and to answer by telephone a few questions about their work situation at 12 months of follow-up. We choose this strategy to be able to comprehend if a selective population of cancer patients have participated in our evaluation study. The participant flow diagram is shown in Fig. 2.

**Fig. 2 Fig2:**
[figure not shown]
Participant flow diagram

### Participants

Eligible for this study will be patients with a primary diagnosis of cancer who will be treated with curative intent at the hospital of recruitment, between 18–62 years old, in paid employment or self-employed and who have sufficient knowledge of the Dutch language. Patients will be excluded if they have a severe comorbidity or if they have no Internet access.

### Sample size

On average, we will include cancer patients at 6 weeks or 42 days after diagnosis, and the follow-up time for the primary outcome return to work will be 12 months after inclusion, hence 12 months and 42 days after diagnosis. Earlier studies in our hospital showed that return to work for patients with various cancer types was 64 % at 12 months of follow-up from diagnosis [28]. In addition, earlier studies in our hospital showed that return to work in the first 42 days is around 8 % [28]. Therefore, the return to work for the control group was set at 64 % + 8 % = 72 %. In a study of Nieuwenhuijsen et al. [29], an intervention group of 35 radiotherapy patients received a supportive work-related intervention in a hospital. Time between diagnosis and the end of treatment was a median 42 days. Return to work was measured between the end of treatment and work resumption and was 89 % after 12 months. Therefore, the return to work for the intervention group in our intervention was also set at 89 %.

Based on our earlier studies on consecutive cancer patients, a power analysis indicated that we should include a total of 170 patients with a follow-up of 1 year after inclusion to indicate a difference of 89 % return to work in the intervention group versus a 72 % return-to-work rate in the control group, with a power of 80 % and *p* < 0.05. Accounting for 10 % loss to follow-up, 190 patients should be included.

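### The 72% control return-to-work rate adds early returns to a cumulative figure that already contains them, so the stated 80% power has no valid basis, though the direction of the error is open

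*Protocol article*

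**What the plan says.** All of this is in the Sample size section of the protocol article unless stated otherwise.

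- **Timing.** On average "we will include cancer patients at 6 weeks or 42 days after diagnosis". The primary outcome is taken 12 months after inclusion, which is 12 months plus 42 days from diagnosis.
- **Control arm.** Earlier hospital data showed that "return to work for patients with various cancer types was 64" per cent at 12 months from diagnosis, and that "return to work in the first 42 days is around 8" per cent. The two are summed: "Therefore, the return to work for the control group was set at 64" plus 8, that is 72%.
- **Intervention arm.** In a cited study, "an intervention group of 35 radiotherapy patients received a supportive work-related intervention in a hospital". Median time from diagnosis to end of treatment was 42 days, and 89% were back at work 12 months after that. "Therefore, the return to work for the intervention group in our intervention was also set at 89" per cent.
- **Size.** 170 patients for 89% versus 72% at 80% power and p < 0.05, raised to 190 for 10% loss.
- **Entry condition.** The Methods part of the abstract describes eligible patients thus: "Patients who have paid employment at the time of diagnosis, are on sick leave". The Participants section lists paid employment or self-employment and does not mention sick leave.

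**The concern.** Return to work by 12 months, counted from diagnosis, is a cumulative proportion. Whoever returned in the first 42 days is inside the 64%, so adding the 8% counts those people twice.

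The aim of the addition is understandable: follow-up ends 42 days later than the historical figure, so some upward adjustment is due. But the amount needed is the return between month 12 and month 12 plus 42 days, and the plan uses the return just after diagnosis instead.

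The population matters too. If patients must be on sick leave when included at about day 42, the early returners are largely outside the trial. They then have to come out of both numerator and denominator.

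At stake is the one power statement for the primary outcome. Readers will use it to judge what a null or positive result means.

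**Working it through.** **1. Reproduce the plan.** Two-sided 0.05 (sidedness is not stated, but this reproduces), 1:1 allocation, normal formula with pooled variance under the null, no continuity correction:

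n per arm = [1.96·√(2p̄(1−p̄)) + 0.8416·√(p₁(1−p₁) + p₂(1−p₂))]² / (p₂−p₁)²

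With p₁ = 0.72, p₂ = 0.89 and p̄ = 0.805, n = 84.1, so 85 per arm or 170 in total. Power at 85 per arm is 80.4%. Loss to follow-up: 170/0.9 = 188.9, about 190. The calculation is right for its inputs; the fault is in the 72%.

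**2. Is 8 points plausible for the last 42 days?** At month 12, 100 − 64 = 36% are still off work. Adding 8 points means 8/36 = 22% of them return within 42 days. For comparison, fit a constant hazard between day 42 (92% off work) and day 365 (36% off work). This is an assumption.

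- h = −ln(0.36/0.92)/323 = 0.00290 per day
- Return in a further 42 days = 1 − exp(−42h) = 11.5%
- Off work at day 407 = 0.36 × 0.885 = 0.319

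So even with early returners kept in, the extended rate is about 68%, not 72%.

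**3. Control rate among those not back at work on day 42.**

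- No returns after month 12: (64 − 8)/(100 − 8) = 60.9%
- Constant hazard to day 407: 1 − 0.319/0.92 = 65.4%
- The plan's further 8% granted in full: (72 − 8)/92 = 69.6%

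All three are below 72%.

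**4. Power with 85 per arm.** The planned pair implies a difference of 17 points, a relative risk of 0.89/0.72 = 1.24, and an odds ratio of (0.89/0.11)/(0.72/0.28) = 3.15. Each cell gives the intervention rate, then the power.

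| Effect held fixed | Control 60.9% | Control 65.4% | Control 69.6% |
|---|---|---|---|
| Difference, 17 points | 77.9%: 67.4% | 82.4%: 71.7% | 86.6%: 76.9% |
| Relative risk 1.24 | 75.2%: 52.0% | 80.8%: 62.3% | 86.0%: 73.5% |
| Odds ratio 3.15 | 83.0%: 90.3% | 85.6%: 87.2% | 87.8%: 83.3% |
| Intervention rate 89% | 89%: 99.2% | 89%: 96.3% | 89%: 88.5% |

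For the 68.1% control rate of step 2 the four powers are 75.0%, 69.5%, 84.8% and 91.9%.

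**5. Precision of the 89%.** The article gives no count. If 89% of 35 is 31 patients, the exact 95% interval is 73% to 97%.

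**The case against.** The strongest reply is that the plan does not target 17 points or a relative risk of 1.24. It takes 89% from a separate study, so correcting only the control arm leaves 89% in place and power rises to between 88.5% and 99%. A fixed odds ratio also gives more than 80%. This stands. A reader might infer from the error that the trial is underpowered, and the documents do not support that: the direction depends on which effect is held fixed.

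A reader might also infer that the 89% runs on a different clock because it is timed from end of treatment. It does not. The median of 42 days from diagnosis to end of treatment, followed by 12 months, matches inclusion at about day 42 followed by 12 months. What remains is a different case mix (radiotherapy only) and 35 patients. That makes the 89% an uncertain assumption, not an error.

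Third, the exclusion of early returners is not settled. Sick leave at entry appears in the abstract only, inclusion at day 42 is an average, and the article does not say whether the historical 8% is full or any return, whereas the primary outcome counts partial return. This stands as a limit on the 61% to 70% range. It does not rescue the sum, since double counting does not depend on it and keeping early returners in still gives about 68%.

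Finally, the source cohort is not visible, and its reference number in the Sample size section is also the one cited for the reporting checklist. The exact rate therefore cannot be fixed from the article.

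**Conclusion.** The point holds as an invalid derivation of a stated figure. On the plain wording, 64% + 8% counts the early returners twice, and none of the alternatives built from the plan's own two numbers reaches 72%. For patients still off work at day 42 the range is about 61% to 70%; about 65% needs the constant-hazard assumption.

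The 80% power is unsupported and holds in none of the scenarios checked. Across them it runs from 52% to 99%: below 80% if the absolute difference or the relative risk is kept, above it if the odds ratio or the 89% is kept. The relative-risk scenario is relevant because the Effectiveness section plans a relative risk with a 95% confidence interval. That interval will show the precision achieved whatever rate was used for planning, so the defect lies in the planning claim and not in the analysis.

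Confidence is high that the sum is wrong and moderate on the size of the correction.

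**What to change.** 1. Replace 64% + 8% by the return-to-work rate at 12 months plus 42 days from diagnosis among patients still on sick leave at inclusion. Derive it from the source cohort, using the trial's definition of return. If that is not possible, give the range 61% to 70% with its assumptions, and correct the reference to the cohort.
2. Reconcile the abstract and the Participants section on whether sick leave is required at entry, since the control rate depends on it.
3. State the target effect and its scale. Show the 89% as an uncertain assumption resting on 35 radiotherapy patients.
4. Replace the single 80% with a short power table for 170 evaluable patients over the control range and the candidate effects, such as the one above.

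The cost is a rewritten paragraph and, at most, a look back at the source data. Enrolment of 190 and the planned analysis can stay as they are. The sponsor gives up a single reassuring figure, and the restated power may be lower or higher depending on the effect chosen.
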